# Protection of persons

## Ethical justification of the protocol

It is research for human pathophysiology and of no benefit to the participants. Research is safe for participants if the exclusion criteria are met.

## Ethical and regulatory provisions

The research will be conducted in compliance with French regulations, including provisions relating to biomedical research of the Code of Public Health, Article L 1121-1 and following the laws of Bioethics, the Data Protection Act, Files and Liberties (including the reference methodology MR-001 on biomedical research - Appendix 10) , of the Declaration of Helsinki (Appendix 9) , and of this protocol.
The investigator agrees to conduct the research in accordance with the ethical and regulatory requirements. He/she is aware that all documents and all data relating to the research may be subject to audits and inspections in respect of professional secrecy and may not be resisted without medical confidentiality. The investigator recognizes that the search results are the property of Inserm, the research sponsor.

## Protection Committee (CPP)

Before the implementation of the research, the sponsor will submit the project to the opinion of the Protection Committee (CPP) of the Hospital Dieu and provide the committee with all the necessary information: research protocol, information form and consent (Annex 2), notebook for observations (Annex 3), questionnaires (Annex 3 and 4) and any other relevant documents to be presented to the Committee.

The test will begin when the laboratory CEPRODI KOT has been informed of the favorable unqualified opinion issued by the CPP about the protocol submitted. This review will include the title and protocol number assigned by the sponsor, the documents reviewed and the date of examination and the list of members of the CPP who participated.

The promoter will inform the CPP of all substantive changes to the protocol and of all serious or unexpected adverse events and developments occurring during the research and affecting the safety of persons undergoing the procedures, in accordance with the procedure described in this protocol.

## Insurance and Finance

The CEPRODI-KOT Laboratory, as a sponsor, has subscribed for the entire duration of the test, an insurance liability contract with the company HDI-Gerling Industries, whose address is [name], under number 200800080, in accordance with French laws and regulations on biomedical research (insurance certificate relevant to this protocol is annexed to the latter).

The insurance certificate relating to this protocol is contained in Annex 6.

The research funding is provided by the INRA (ANR Research Programme 2008-2011).

## Procedures for obtaining subject consent

Written informed consent of all people who participate in biomedical research must be obtained by the investigator, registered in the order of medical doctors, declared as an investigator with the sponsor before any act can be performed under the research protocol and whatever the act, in accordance with the Public Health Code, Article L1122-1.

Information will be given orally and in writing in the first part of the form of information and consent (Annex 2). The form will be signed at the bottom of each page so that the person suitable for the research confirms receipt of this information. The information is written in plain language understandable to the person. It must contain all the elements that the person must be informed about, in accordance with the Public Health Code, Article L. 1122-1.

The consent of the subject participation in research is collected in writing on the second part of the information and consent form. This second part should be written in clear, understandable language for the person undergoing the research. It must contain all the elements that the person consents. Consent is given by affixing the signature and inscription, from the hand of the person who is willing to take part in the research, first name, last name and date of consent.

In addition, the investigator collects dates and sign the consent form in the position reserved for him and ensures 1) that the form is accurate and no information or date is missing, 2) that an original copy of the document is given to the patient. The investigator maintains a second copy in a safe place and to which access is controlled and 3) a third original copy is placed in a secure location for the attention of the sponsor. The third copy shall not be opened by the sponsor, but retained with the permanent records of the study.

The investigator must ensure that the person is suitable for the research will have time to make a decision freely and be able to read and understand the information form and consent.

The information form and consent is a document that has been approved prior to the implementation of research by the CPP, on the occasion of the review of the protocol.

The participation of people in this protocol shall be registered on the national register of persons undergoing biomedical research, managed by the Ministry of Health.

## Compensation

It is 500 Euros, this amount will be paid at the end of the study, after 12 weeks of participation. If the subject is required to stop the study before completion, no compensation will be paid pro rata.

# ObjectiVEs

**MICRO-Obes** aims to characterize the relationship between intestinal microbiota and the nutritional, inflammatory and metabolic status of the host before and after calorie restriction of 1200 Kcal for 6 weeks followed by a stabilization phase 6 weeks among obese.

**1. A nutritional and metabolic approach will be conducted to assess:** 1) weight loss, 2) reduction of fat mass and adipocyte size, 3) markers of systemic inflammation (CRP-us, IL 6, SAA), 4) plasma lipids, plasma glucose and insulin, 5) the insulin sensitivity, 6) changes in gene and protein expression in adipose tissue (500 mg by suction under local anesthesia with a fine needle) of inflammation factors characteristic of adipocytes and macrophage infiltration.

**2. A metagenomic approach** will also be implemented in order to sequence the dominant genetic repertoire of human intestinal microbiota (stool samples) and identify the functions of the relevant host-microbiota dialogue in capturing energy from food.

# expérimental PLAN

## Type of test

It is to search human pathophysiology. This is a study without direct individual benefit, in obese subjects.

## Category of research :

## Physiopathological study

## Presentation of the experimental design (CF Schéma général : page 2)

A population of 50 obese subjects will be selected after a review of pre inclusion.

After inclusion, subjects follow a low calorie diet of 1200 Kcals for 6 weeks followed by a stabilization phase of 6 weeks. The low calorie diet will be provided and delivered by the laboratory CEPRODI-KOT (attached a list of products offered and a standard menu with products CEPRODI-KOT). Dietary advice will be given at the beginning of each period, patients will be contacted in the middle of each period and a dietician will always contactable by phone or email. The dietician will contact the patient by phone once a week to ensure that there are no difficulties. Data collection will be done at the beginning and end of each period using a food diary kept for one week. The food composition (nutrients) is obtained using a French food composition table.

The stabilization phase of weight will be adjusted depending to the resting energy expenditure (REE) of each patient and will be calculated by the dietician according to the formula of Harris and Benedict :
REE man = 66.473 + (5.003 x height in cm ) + (13.752 x weight in kg) - (6.755 x age)
REE Woman = 655.096 + (1.850 x height in cm ) + (9.563 x weight in kg ) - (4.676 x age)

**Justifications for the selection of a restriction to 1200 kcal for 6 weeks:**

Weight loss by "only" dieting is significant when energy intake is typically significantly lower than energy expenditure. In this study, it will be recommended for subjects to continue their usual level of physical activity. Schemes commonly used in the clinic or in clinical investigation programs are threefold: very low calorie diet (VLCD or very low calorie diet <800 kcal, intermediate (LCD or low calorie diet 800-1500 kcal per day) or very moderate (500 kcal less than usual intakes). Such approaches to the medical management of obesity have been the subject of a recent review in the New England Journal of Medicine (11).

The choice of intermediate diet and duration is based on several arguments: 1) the absence of " risk " associated with a very low calorie diet (VLCD) requiring special monitoring including vitamins and potassium, 2) induction of a slope of rapid weight loss: in previous programs in the team (Project: Effect of two different hypocaloric diets on weight loss and on inflammatory markers) and European programs (**NUGENOB and DIOGENES**), we were able to evaluate this aspect, in agreement with other teams, as weight loss is induced faster in this type of low calorie diet compared with the moderate diet and becomes significant at around 5-6 weeks (eg Figure 1), 3) the feasibility of these programs: these " low calorie diets" were used repeatedly by our team ( Project of [name]: Effect of two different hypocaloric diets on weight loss and on inflammatory markers) and are well tolerated by the subjects that are regularly monitored by the dietitian in accordance with the recommendations, 4) the observation of a transition of the bacterial flora switch firmicute / bacteroides observed at the limit of significance in a pilot study by our collaborator ANR ([name]).

Therefore we selected a six week diet as the point where even the poor responders monitored under a European project lost about 6% of their initial weight. This is consistent with the work of Gordon Group (12).

**Scientific justification for the 6 weeks of the stabilization phase:**

One of the difficulties of low calorie diets is weight regain after stopping energy restriction and multiple mechanisms involving dialogue inter organ (brain adipose tissue) are set up for a return to the previous weight (11). The predictors of weight maintenance involves the maintenance of a low fat diet, frequent and individual control weight and food intake may be supported by regular advice from a dietician and maintenance of level of physical activity (11).

These techniques will be used to maintain weight loss called the stabilization phase. Maintaining the stabilization phase depends heavily on understanding and adherence to dietary advice. In the previous project (***effets de deux régimes hypocalorique sur la perte du poids et sur les marqueurs de l’inflammation***)), we observed that advice helped a weight maintenance for 8 weeks in 11 of 15 subjects followed. We will continue the one-month follow-up in order to give more opportunities for subjects to maintain their long-term weight gain and use behavioral advice (13).

# évaluation CRITERIA

**Main criteria:**

• Quantification of body weight loss and the loss of total body fat
• Variation in the microbiota Firmicutes / Bacteroidetes
• Quantification of the reduction of systemic inflammation (CRP -us , IL6 , TNF , serum amyloid )
• Analysis of profiles of gene function ( gene regulatory networks analyzed by microarray ) interacting with inflammatory functions in the kinetics of weight loss
• Quantification of macrophage infiltration by gene and protein markers (CD11b CD68, and pro markers (CD40) or anti- inflammatory (CD163, mannose receptor)): in the subcutaneous adipose tissue before and after weight loss and linking with the reduction of systemic inflammation (CRP -us, IL6, TNF, serum amyloid).
• Analysis of interactions between the changes of the intestinal flora, biological variations and adaptations (including inflammatory) adipose tissue.

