### Number of people to include:

Effective Calculation: 50 subjects are required to show a change in the ratio of microbiota Firmicutes / Bacteroidetes of at least 40% and a standard deviation of 16 by setting the risk to   0.05 and the risk to 0.10 (calculations made after the results of a pilot study with a low calorie diet of 1200 Kcal).

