# Practical realization of the study

## Detailed description for the acts realised on the participants:

**Nutritional and inflammatory profiles**

We will evaluate lipid profiles and the glycemic contrôle of subjects before and after each periode. At each time point after overnight fast.at 8h00, blood samples will be taken for measurements plasma glucose, insulin, total cholesterol, LDL- and HDL-cholesterol, triglycerides, leptin and adipnectin.Inflammatory markers: CRPus, and IL6 will be also measured by radio immunologic method or by ELISA) and plasma LPS.

Insulin sensitivity will be estimated by a an oral glucose tolerance test after a charge of 75g of glucose .Blood samples will be taken at 30 min , 60 min et 120 min to measure plasma glucose and insulin..

Body fat and fat-free mass distributions were measured using dual-energy X-ray absorptiometry (Hologic APEX, discovery W. (S/N 84030), version 3.0, Bedford, MA

An sample of subcutaneous abdominal adipose tissue will be taken by aspiration with a fine needle under local anaesthesia (1% xylocaine without isoprenalin).

Two supplementary tubes of blood (7 ml) will be taken to measure other new markers that will be identified by the transcriptomic approch

After 7days of the beginning of the dietary program one tube of blood (1 tube of 10 ml) and an adipose tissue biopsy will be taken to evaluate the early kinetic changes of weight loss and the inflammatory markers in adipose tissue.

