Results from cDNA microarrays will be analyzed by the Inserm Unit U872 (Team 7), where new strategies of oligonucleotide microarray data analysis are being developed. Experimental results will be stored in the SMD database (http://genome-www5.stanford.edu). We will use a certain number of functions developed for R software (steps of filtering, normalization, selection of differentially expressed genes, groups, etc) in order to highlight groups of modified genes. The translation of gene expression data into the corresponding biological mechanisms (commonly called functional analysis or profiling) is considered a major challenge and is an essential step in the elucidation of the biological phenomena underlying the experimental models being studied. Functional annotation will be used to connect sets of genes in the genome with molecular networks that interact within the cell, in order to illustrate the higher order biological information related to metabolic pathways and their regulation. We will search automatic descriptions of enrichment through the databases Gene Ontology (GO) or KEGG (Kyoto Encyclopedia for Genes and Genomes). Our functional analysis will essentially be centered on inflammatory factors and their associated gene networks. Two algorithms, MAGO and FunCluser, have already been designed with this in mind by our team. They automatically link gene transcription microarray data with the genes’ biological roles in order to investigate significant functional changes in the experiment compared to other functions represented on the chip. We will introduce appropriate statistical analysis to take into account multiple testing (False Discovery rate). A computer engineer in the U872 Inserm team will be dedicated to the work of microarray analysis.

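### Six unranked main criteria naming at least 12 measures, while the sample size rests on the Firmicutes/Bacteroidetes ratio alone and no visit is fixed for it

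*Protocol*

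**What the plan says.** The evaluation criteria section of the Protocol has a heading "Main criteria" with six bullets and a separate heading for secondary endpoints with one. The main bullets carry no order, and nothing says how many must succeed. They are:

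1. "Quantification of body weight loss and the loss of total body fat" (2 measures)
2. "Variation in the microbiota Firmicutes / Bacteroidetes" (1 measure)
3. "Quantification of the reduction of systemic inflammation (CRP -us , IL6 , TNF , serum amyloid") (4 measures)
4. gene-function profiles from microarrays (number of tests not given)
5. macrophage infiltration by CD11b, CD68, CD40, CD163 and the mannose receptor, as gene and protein markers (5 named markers, up to 10 measures)
6. interactions between flora changes, biological changes and adipose tissue (number not given)

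The section on the number of people to include uses the second bullet only: "50 subjects are required to show a change in the ratio of microbiota Firmicutes / Bacteroidetes of at least 40" per cent, with a standard deviation of 16 and risks of 0.05 and 0.10. It names no visit. The visit table in the Overview schedules the faecal assessment at Days 0, 42 and 84.

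Part A of the statistical section names MANOVA over time, ANOVA, ANCOVA and logistic regression. It gives no rule across the main criteria. The only multiplicity statement is in the expression studies text: "We will introduce appropriate statistical analysis to take into account multiple testing (False Discovery rate").

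The inflammatory markers vary by section. The visit table and the main criteria have CRP, IL6, TNF and SAA. The Objectives have "markers of systemic inflammation (CRP-us, IL 6, SAA"). The practical section has "Inflammatory markers: CRPus, and IL6 will be also measured", followed by plasma LPS.

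**The concern.** The sample size section treats one criterion as the decisive one, while the criteria section gives it the same rank as five others. The reader cannot tell which result answers the trial's main question.

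This has a practical side. In justifying the diet, the Protocol reports that the shift in flora was only at the limit of significance in a pilot study. An F/B result that misses significance while some other main measure moves is therefore a realistic outcome. As written, that other measure could be reported as a main result at face value, and the visit used for the F/B change could be settled after the data are seen.

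**Working it through.** **The plan's own figure.** The Protocol states 50 subjects for a 40% change, SD 16, with the two risks read as alpha 0.05 and power 90% (the symbols are lost in the text, and sidedness is not given). For a within-subject change, n = (SD × (z_alpha + z_beta) / change)².

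- 40 and 16 in the same unit, two-sided: (16 × 3.242 / 40)² = 1.7. The t-distribution needs 4 to 5 subjects (power 89.9% at 4, 98.2% at 5).
- 40% read as 0.4 SD: 65.7 two-sided, 53.5 one-sided.

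None of these gives 50. That is a separate matter. The present point needs only the fact that F/B is the sole criterion used for sizing.

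**Number of named measures.** 2 + 1 + 4 + 5 = 12. Counting gene and protein separately for the macrophage markers gives 17. Microarray profiles and associations are left out because the Protocol gives no count.

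**Chance of at least one false positive**, each measure tested at 5% and all nulls true. Under independence it is 1 − 0.95^m. The correlated figures come from a simulation of m equally correlated normal test statistics (200,000 draws, two-sided 5%). The correlations are assumptions, since the Protocol gives none.

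| Measures | Independent | 0.3 | 0.5 | 0.7 |
|---|---|---|---|---|
| 12 | 46.0% | 39.7% | 32.0% | 23.2% |
| 10 (without weight and fat) | 40.1% | 35.1% | 28.6% | 21.4% |
| 17 | 58.2% | 49.4% | 38.8% | 27.1% |

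Under independence the figure first passes 50% at 14 tests (1 − 0.95^14 = 51.2%). Testing each measure at both Day 42 and Day 84 would raise all these figures. The Protocol does not say that the visits are tested separately, so no number is put on that.

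**What keeping all of them primary would cost.** At two-sided 5% and 90% power, 50 subjects detect a standardised change of (1.960 + 1.282) / √50 = 0.458 SD. Holding that effect under Bonferroni:

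- six criteria, 0.05/6 = 0.0083 each: ((2.638 + 1.282) / 0.458)² = 73.1, so 74 subjects
- 12 measures, 0.05/12 = 0.0042 each: ((2.865 + 1.282) / 0.458)² = 81.8, so 82 subjects

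With F/B as the only primary criterion, the primary error rate is 5% and multiplicity calls for no more subjects.

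**The case against.** The strongest reply is that this is a single-group pathophysiological study meant to characterise relationships. It states no rule for calling the trial positive, and a single primary endpoint is a convention of confirmatory trials. A multiplicity procedure, and perhaps the visit for the contrast, could also sit in a statistical analysis plan that is not shown. This lowers the stakes but leaves the mismatch. The Protocol itself separates main from secondary criteria and itself sizes the trial on one main criterion with stated error risks. Which criterion leads is a decision made in this document.

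Several stronger readings are tempting and should be resisted:

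- **That there is no error control.** The false discovery rate is promised for the microarray data, which is the fourth main criterion. What is missing from the text is control for the others and across the list.
- **That a positive main result is likely by chance.** For the 12 named measures the figure is below one half even under independence. It also assumes every null is true. The diet justification reports that even poor responders lost about 6% of initial weight by six weeks, so a fall in weight, and in fat with it, would not be a chance finding.
- **That each measure is planned as a separate 5% test at each visit.** The Protocol names MANOVA over time. This is not a rule across criteria, but it is not a series of separate tests either.
- **That false positives among flora-host associations can be counted.** Seven bacterial groups are mentioned, but no number of host markers, and clustering and multivariate analysis are planned.
- **That TNF goes unmeasured.** The visit table schedules it at Days 0, 42 and 84. Its absence from the Objectives and the practical section is a drafting inconsistency, and the practical section omits SAA as well.

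**Conclusion.** The point holds in limited form. Six main criteria of equal rank, naming at least 12 measures, stand against a sample size built on the F/B ratio alone, with no visit fixed for that ratio and error control stated only for the microarray data. If each of the 12 were tested at 5%, the chance of at least one false positive would be roughly 23% to 46%, depending on correlation. For the 10 measures without weight and fat it would be 21% to 40%. These figures rest on all nulls being true, on separate 5% tests, and on assumed equal correlations from 0 to 0.7. They show what the unranked list allows and do not describe a stated testing plan. Even the lowest is more than four times the nominal 5%. The change is worth making because it is cheap. The exploratory nature of the study keeps the point from being more serious.

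**What to change.** - Name the change in F/B ratio from Day 0 to Day 42 as the single primary criterion, tested at two-sided 5%. Day 42 ends the 1200 kcal phase, and the sample size is said to come from a pilot on that diet.
- Make the other five main criteria secondary. Extend the false discovery rate control already planned for the microarray to them and to the flora-host associations.
- As a minor drafting point, align the inflammatory marker lists in the Objectives and the practical section with the visit table and the main criteria (CRP, IL6, TNF, SAA).

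The cost is wording in the Protocol and the analysis text. No extra visits, samples or, as far as multiplicity goes, subjects are needed. The downside is that claims on weight, fat, inflammation, macrophage markers and gene profiles become secondary. If the sponsor prefers to keep several criteria primary, the Protocol should state the rule across them and size the trial for it. Under Bonferroni, that means about 74 subjects for six criteria or 82 for 12 measures, at the effect that 50 subjects now detect with 90% power.
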